### Sample size calculation

A total of 258 women will be enrolled in the study. The sample size was determined using unpublished data on 426 pregnant women with chronic diseases hospitalized at Rigshospitalet during pregnancy and in the postpartum period in 2017. The average LOS during pregnancy was 3.9 days; however, due to a right-skewed distribution, log-transformed LOS was used as the outcome for the sample size calculation. Therefore, the effect of the intervention is expressed as a ratio. We expect a reduction of 25% in LOS in the intervention group compared with the control group. This corresponds approximately to a mean reduction of 1 day of hospitalization and to an improvement of log (1 – 0.25) = − 0.29 on the logarithmic scale, which we consider a realistic and clinically significant effect size. The standard deviation (SD) of number of days in the hospital on a logarithmic scale was 0.80. With a difference of 0.29 and SD of 0.80, a power of 0.8, and a significance level of 0.05, an analysis by two-sample *t* test requires 123 women in each group. We expect a maximum of 5% to be lost to follow-up, leading to a total of 129 women needed to be enrolled in each group (Fig. 1).

**Fig. 1 Fig1:**
[figure not shown]
The expected flow diagram of progress through the ChroPreg trial

### Intervention

#### Standard care alone

Participants allocated to the control group will receive standard care alone. Pregnant women with chronic disease are considered to have high-risk pregnancies and are referred to the appropriate level of specialized maternity care. All pregnant women with chronic disease will be followed by an obstetrician, and an individual care plan is designed considering the character and severity of the disease and the pregnancy-associated risks. Routinely in Denmark, all pregnant women, including pregnant women with chronic diseases, are also followed by midwives during pregnancy. The standard care appointments for midwife consultation are timed approximately around weeks 14–18, 28, 35, 38, and 40 and include physical examinations, discussion about lifestyle, symptoms of normal and complicated pregnancies, breastfeeding, and preparation for delivery. At Rigshospitalet, two auditorium prenatal classes (90 min each) are delivered by a midwife. The classes provide information about what to expect during birth (contractions, pain relief, possible complications, and interventions) and in the puerperium (breastfeeding and family building). After childbirth, women can contact the department and request a conversation about the delivery with a midwife, and women who have experienced severe or unexpected complications may be offered a postnatal consultation with an obstetrician.

#### ChroPreg intervention plus standard care

The ChroPreg intervention is designed on the basis of a review of the literature on complex interventions in maternity care [19–21] and is aimed to fit the needs of women with chronic disease. Complex interventions [32] consist of a number of components that may work independently and interdependently, and it can be difficult to identify the “active ingredient” of the intervention, rendering it even more important to describe the different components, the hypothesized mechanism behind each component, and the interaction between the components [32]. The three main components of the ChroPreg intervention are described in more detail below.

The ChroPreg intervention is provided by SM. In addition to the standard care outlined above, women in the intervention group will receive additional antenatal consultations, postpartum follow-up, and care coordination. Both standard care midwife consultations and the extra consultations will be provided by the same SM (content described below and in Table 1).

**Table 1 Tab1:** Description of planned midwife activities in the ChroPreg intervention group and standard care group

ChroPreg intervention + standard care	Objective of activity	Standard care alone	Objective of activity
During pregnancy			
*Weeks 14–18* Midwife appointment 30 min Specialized midwife (SM) At the hospital	Medical history taking, follow-up on information from general practitioner	*Weeks 14–18* Midwife appointment 30 min Regular midwife (RM) At the hospital	Medical history taking, follow-up on information from general practitioner
*Weeks 20–24* Midwife appointment 60 min SM At the hospital	Focus on psychological well-being during pregnancy and preparation for breastfeeding. The consultation will be centered on the woman’s experience of pregnancy, physical development, prenatal attachment, the interaction between pregnancy and chronic disease, normal pregnancy signs and symptoms, and thoughts about breastfeeding.		
*Weeks 28–30* ^a^ Midwife appointment 30 min SM At the hospital	Conversation about breastfeeding, rhesus prophylaxis, well-being, and symptoms of pregnancy and chronic disease.	*Weeks 28–30* Midwife appointment 30 min RM At the hospital	Conversation about breastfeeding, rhesus prophylaxis, well-being, and symptoms of pregnancy
*Weeks 30–33* Midwife appointment 60 min SM At the hospital	Focus on individual childbirth preparation and postpartum care. Information about birthing options and pain relief and management. The individual needs and wishes of the woman will be discussed, and an individual birth plan will be made.		
*Weeks 35–36* Midwife appointment 30 min SM At the hospital	Consultation about pregnancy, well-being, symptoms of chronic disease, and the coming birth.	*Weeks 35–36* Midwife appointment 30 min RM At the hospital	Consultation about pregnancy and the coming birth, and well-being.
*Weeks 38–39* Midwife appointment 30 min SM At the hospital	Consultation about pregnancy, well-being, symptoms of chronic disease, the coming birth, and postpartum care and follow-up.	*Weeks 38–39* Midwife appointment 30 min RM At the hospital	Consultation about pregnancy, coming birth, and postpartum care
*Week 40* Midwife appointment 30 min SM At the hospital	Consultation about coming birth, pregnancy, and signs of labor, discussion about induced labor Internal vaginal examination if woman wishes	*Week 40* Midwife appointment 30 min RM At the hospital	Consultation about coming birth, pregnancy, and signs of labor; discussion about induced labor Internal vaginal examination if woman wishes
Postpartum follow-up			
*First and second weeks after discharge from hospital* 30–60 min SM Telephone	Postpartum follow-up on breastfeeding, chronic disease management, medication, and psychological well-being. Coordination with primary health care workers if needed (general practitioner/health visitor/medical specialists).	*First week after discharge from hospital*	The woman can contact the hospital with questions and need for postpartum check-up.
*4–6 weeks postpartum* *60 min* Midwife appointment SM At the hospital/telephone (woman’s choice)	This visit is arranged for the woman to have the opportunity to discuss her experiences of pregnancy and childbirth with the SM. The midwife will have the medical records available, but the focus is on allowing the woman to talk about and elaborate on her experience. If the midwife and the woman identify a need for further counseling, referral can be made to a psychologist.	*After discharge from hospital*	The woman can contact the department for an appointment to discuss experiences of pregnancy and childbirth.
Activities throughout the study period			
*E-mail correspondence* From inclusion to end of study period SM	The woman can contact the SM by e-mail. This contact may concern all relevant issues during pregnancy and postpartum.	*E-mail correspondence*	No e-mail correspondence included. Women can contact the coordinating midwife department with questions and concerns
*Weekly telephone hours* From inclusion to end of study period SM	One day each week, the SM will be available for telephone consultation as a supplement to the planned face-to-face consultations. Participants can call the midwife with questions or concerns. The midwife will evaluate if further visits will be needed in addition to the telephone contacts.	*Telephone correspondence*	Women can contact the coordinating midwife department with questions and concerns.

^a^All standard midwife appointments from week 28 onward include urine testing for glucose and protein and measuring of blood pressure (screening for indicators for gestational diabetes and preeclampsia) and physical examinations (measuring the size, heartbeat, and position of the fetus)

##### Midwife-coordinated and individualized care

The participant will be seen by the same SM throughout the study period. For all women in the intervention group, the number of consultations covered by the SM will be recorded. During the study period, the SM will identify the special needs and wishes of each woman and will discuss the optimal care of the woman with the obstetrician responsible for her medical care. The SM will assist the participants in coordinating antenatal visits to fit their everyday life and to avoid unnecessary hospital visits, as well as in communicating with other care providers who are part of the standard Danish health care system (e.g., general practitioner and health visitor) as well as other health care professionals from other departments at the hospital. The participants can contact the SM by e-mail and during weekly phone hours. If the participant is hospitalized during pregnancy, the SM will contact the woman by phone and arrange an appointment. Assisting the participants when in labor is not a part of the intervention.

##### Additional ante- and postpartum consultations

In addition to standard care, two additional antenatal consultations will be scheduled with the SM at 20–24 weeks and 30–33 weeks of pregnancy to discuss psychological well-being in pregnancy, breastfeeding, individualized preparation for childbirth, and postpartum care. The purpose is to support the woman’s own capacity to handle her pregnancy, childbirth, and everyday life as a new mother with a chronic disease. If the need arises, the SM can refer the woman to a psychologist at the hospital for additional consultation. After birth, the SM follows up with the woman regarding psychological well-being during the planned telephone support postpartum, and 4–6 weeks after birth, a consultation is planned with the SM to discuss the woman’s overall experience and issues important to the woman regarding her pregnancy and delivery.

##### Specialized midwives

Before initiation of the study, the SM will have all attended a 3-day training delivered by medical specialists from the hospital handling the care for pregnant women with various chronic diseases. The training includes medical knowledge on systemic lupus erythematosus, rheumatoid arthritis, lung disease, kidney disease, hypertension, multiple sclerosis, epilepsy and other neurological diseases, inflammatory bowel disease, hematological diseases, and thyroid disease. Additional topics in the training program are prepregnancy counseling, pathophysiology, pregnancy complications, symptoms of disease in relation to pregnancy, obstetric treatment, medication and drug safety, lactation, and interdisciplinary collaboration. The training also includes psychological aspects of pregnancy complicated by chronic disease. Topics covered are psychological development during pregnancy, signs and symptoms of depression and anxiety during pregnancy and postpartum, prenatal attachment, and facilitating conversations about the woman’s experience of childbirth. This part of the training is delivered by midwives with further education in psychology and by clinical psychologists. A manual that outlines the content of all consultations with the SM and topics covered during the consultations will be developed and used as a tool by the SM. To secure intervention fidelity, observations of the SM consultations are carried out by one of the investigators in order to give feedback.

### Outcome measures

Data will be collected from medical records and electronic self-administered questionnaires and will be obtained at baseline (t1) and three times during the study period: at 33–37 weeks of gestation (t3), at 2 weeks after delivery (t4), and at 2 months after delivery (t5) (Fig. 2). The participants will complete the first electronic questionnaire after signing the informed consent to participate and before randomization. The subsequent questionnaires will be sent as a link in an e-mail.

**Fig. 2 Fig2:**
[figure not shown]
Consolidated Standards of Reporting Trials (CONSORT) diagram showing time points of enrollment, intervention, and outcome measures

#### Primary outcome

The primary outcome is LOS measured as the number of days (mean and SD) spent in the hospital from inclusion in the study and until 2 weeks after delivery. All participants are expected to have a minimum of 1 day of hospital stay in relation to the delivery, because this population is a high-risk population in which home birth is advised against. Should a woman nevertheless have an unplanned home birth, she will expectedly be transferred to the hospital for postpartum.

LOS was chosen as the primary outcome because it is a widely used outcome in health care research [33, 34]. For this trial, a reduction in LOS covers at least two important outcomes in health care research: (1) the patient perspective with a reduced need for hospitalization, which is an expression of better quality of health care received by the patients, and (2) the health economics perspective with reduced health care costs in connection with days of hospitalization.

#### Secondary outcomes

##### Psychological well-being

*Five-item WHO Well-Being Index (WHO-5)* [35] measures current (e.g., preceding 2 weeks) psychological well-being and consists of five positively phrased items, each scored on a Likert scale (0 = none of the time, 5 = all the time). The raw score ranges from 0, indicating the lowest possible well-being, to 25, indicating the highest possible well-being. This score is multiplied by a factor of 4, creating a score ranging from 0 to 100, with 100 being the highest possible well-being. WHO-5 has high psychometric validity, and it can be used as an outcome measure in clinical trials [35].*Edinburgh Postnatal Depression Scale* (EPDS) [36] is a self-reported scale consisting of ten items scored on a 4-point Likert scale (0–3) concerning intensity of depressive mood and symptoms during the last 7 days (0 indicates absence of depressive mood and/or symptoms, and 3 indicates the worst mood and/or symptoms on a given item). The lowest overall score is 0, and the highest overall score is 30 (cutoff scores included will be ≥ 10 and ≥ 13) [36, 37]. The EPDS has been validated for use as a detection tool for antenatal and postnatal depression [37, 38], and it has been translated into Danish [39].*Cambridge Worry Scale* (CWS) [40] measures pregnant women’s degree of worry during pregnancy. The questionnaire consists of 16 items concerning different areas of possible worry on a 6-point Likert scale (0 = no worry, 5 = highest degree of worry). The scale ranges from 0 to 60, with 60 indicating the highest possible level of worry. CWS has a high internal validity and reliability and has been used in clinical studies including populations of women with high-risk pregnancies [41, 42].

##### Health-related quality of life and self-rated health

*SF-12* [43] is an abridged version of the 36-item Short Form Health Survey developed to measure health-related quality of life and thereby self-rated health in a single item. The instrument is well-validated and reliable and is widely used, including during pregnancy and in the postpartum period [43, 44] . The SF-12 questionnaire consists of 12 items that measure physical and mental health, divided into eight subscales: physical and social functioning, role limitation due to physical and mental health, bodily pain, general health perceptions (self-rated health), vitality, and mental health. The scores derived from the subscales can be calculated in two overall scores—Physical Component Summary and Mental Component Summary—with higher scores indicating better health-related quality of life [43].

##### Patient satisfaction

The *Pregnancy and Childbirth Questionnaire (PCQ)* [45] contains two subscales: (1) pregnancy-related items (18 items) covering two domains (personal treatment and patient education/information) and (2) birth-related items (7 items). The PCQ consists of 25 items rated on a 5-point Likert scale (1 = totally agree, 5 = totally disagree). Higher scores indicate higher patient satisfaction with quality of care. The questionnaire has been rated to have good internal consistency and reliability [46].

##### Health economic outcomes

Antenatal contacts will be measured as number of scheduled and unscheduled visits with obstetric doctors and midwives and telephone consultations.

##### Pregnancy and delivery outcomes

Pregnancy and delivery outcomes will be measured as pregnancy complications (gestational diabetes, pregnancy-induced hypertension, preeclampsia) (yes/no), labor onset (spontaneous or induced), preterm delivery (yes/no), mode of delivery (percentage of participants with spontaneous vaginal delivery or cesarean section [planned or emergency]), use of labor analgesia (no analgesia/any analgesia, epidural analgesia [yes/no]), outpatient telemonitoring for pregnancy complications (yes/no and duration [days]), newborn’s well-being at time of delivery (Apgar score ≤ 7 at 5 min postpartum [yes/no]), newborn’s birth weight (measured in kilograms), breastfeeding (intention to breastfeed [yes/no], breastfeeding 2 months after delivery [yes/no], and intended duration [in months] of breastfeeding).

### Data analysis

Analyses are to be performed on the basis of the intention-to-treat principle. The log-transformed number of days in the hospital in the two groups will be compared in the primary unadjusted analysis, and in a secondary analysis, adjustments will be made for parity and age. Analysis will be performed using the general linear model unless we find a generalized linear model (e.g., Poisson or negative binomial) to fit the distribution of the number of days in the hospital. Furthermore, the two groups will be compared with respect to the proportion of women with 3 or fewer days in the hospital. Comparison of secondary and exploratory outcomes will similarly be performed using the general or generalized linear models as appropriate. In case of an uneven allocation of pregnancies with congenital malformations or chromosomal abnormalities to the two groups, analyses will be performed in the subgroup of women without pregnancies with congenital malformations or chromosomal abnormalities.

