### Randomization and blinding

After informed consent is obtained, participants are randomized by one of the investigators to either the ChroPreg intervention plus standard care or standard care alone in a ratio of 1:1. The allocation sequence is computer-generated and nonstratified with varying block sizes concealed to the researchers. The allocation will be centrally conducted using the EasyTrial online clinical trial management and randomization system (easytrial.net, Aalborg, Denmark). After allocation, the participants will be informed about the allocation and further plan of the trial.

The specialized midwives (SM) who will deliver the intervention will not be blinded to the allocation, and neither will the participants. However, the research staff who will collect data from medical records and questionnaires will be blinded to treatment allocation, as will the chief investigator ([name]) and the trial statistician (SR).

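### Making the parity- and age-adjusted model of log length of stay (LOS) primary would be a modest, nearly free gain in precision over the valid unadjusted comparison now planned

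*Protocol article*

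**What the plan says.** The Data analysis section ranks two analyses of the primary outcome. Log-transformed days in hospital are "compared in the primary unadjusted analysis, and in a secondary analysis, adjustments will be made for parity and age". The model is linear by default: "Analysis will be performed using the general linear model unless we find a generalized linear model" such as Poisson or negative binomial to fit the distribution. Parity and age are the only covariates the section names, and it gives no reason for putting the adjusted model second.

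The section Randomization and blinding says: "The allocation sequence is computer-generated and nonstratified with varying block sizes concealed to the researchers". The design therefore does not balance parity or age, and equally there is no stratification factor that the primary model ought to contain.

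The Sample size calculation section uses the same unadjusted comparison, a two-sample t test on log LOS. It states "We expect a reduction of 25% in LOS in the intervention group compared with the control group" and "The standard deviation (SD) of number of days in the hospital on a logarithmic scale was 0.80".

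**The concern.** The plan selects two covariates, both known before randomization, and then leaves them out of the confirmatory test. In a linear model with randomized arms, the adjusted and unadjusted coefficients for arm estimate the same difference in mean log LOS, and so the same ratio. The common worry that adjustment changes the question does not arise here. What changes is the residual variance, together with a correction for whatever imbalance in parity or age arises by chance.

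What is at stake is some precision. The trial is sized for 80% power on an assumed 25% reduction and on an SD from one year of data at one hospital. If either assumption is optimistic, a cheap reduction in residual variance is worth having.

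**Working it through.** **Inputs from the article (Sample size calculation).** Ratio 0.75, so the log difference is δ = −ln 0.75 = 0.2877, which the article rounds to 0.29. SD on the log scale 0.80, power 0.8, significance level 0.05, 123 evaluable women per group. The article does not state sidedness; I take two-sided, which reproduces its figure.

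**Input not in the article.** R², the share of the variance of log LOS explained by parity and age together. I use 0 to 15% as an assumed range.

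**Step 1: reproduce the plan's own figure.** The exact two-sample t test (noncentral t) with δ = 0.2877 and SD 0.80 needs 122.4, so 123 per group, as stated. The rounded 0.29 would give 121. Power at 123 per group:

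- standard error = 0.80 × √(2/123) = 0.1020
- noncentrality = 0.2877 / 0.1020 = 2.82 on 244 degrees of freedom
- power = 80.2%

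The unadjusted analysis therefore has the power it was planned to have.

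**Step 2: power after adjustment.** Residual SD = 0.80 × √(1 − R²). The equivalent unadjusted sample size per group is 123 / (1 − R²).

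| R² (assumed) | Residual SD | Power at 123 per group | Equivalent unadjusted n per group |
|---|---|---|---|
| 0 | 0.800 | 80.2% | 123 |
| 2% | 0.792 | 81.0% | about 126 |
| 5% | 0.780 | 82.2% | about 129 |
| 10% | 0.759 | 84.2% | about 137 |
| 15% | 0.738 | 86.1% | about 145 |

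The gain is 2 points or less up to R² = 5%.

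**Step 3: cost if the covariates explain nothing.** Two extra coefficients take the residual degrees of freedom from 244 to 242, and power stays at 80.2%. Estimating those coefficients also inflates the variance of the arm effect by roughly 2/242 = 0.8% on average, which the table ignores. That is the mirror image of an R² of about 0.8%, so adjustment breaks even at about that value. Simulation at R² = 0 (4,000 runs, difference 0.29) gave power of 80.7% unadjusted and 80.0% adjusted, consistent with a loss of a fraction of a point.

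**Step 4: type I error.** Simulated rejection rates under no effect, unadjusted and adjusted (4,000 runs each):

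- R² = 0: 5.6% and 5.6%
- R² = 5%: 5.5% and 5.4%
- R² = 10%: 4.4% and 4.8%

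Both analyses hold the level to within simulation error.

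**Step 5: chance imbalance.** For a covariate with R² = 5%, an imbalance of k standard errors shifts the log difference by √0.05 × 0.80 × k × √(2/123). That is 0.023 for k = 1 (ratio 1.02) and 0.045 for k = 1.96 (ratio 1.05), against a planned effect of 0.29.

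**The case against.** The strongest reply is that nothing here is wrong. The primary analysis and the sample size calculation match, the 123 per group reproduces, and no stratification factor is omitted. Chance imbalance is already allowed for in the type I error and confidence interval of the unadjusted test. The adjusted analysis is pre-specified, so its protection is ranked second, not absent. All of that stands.

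Three further replies also stand.

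- The gain rests on an R² that the article does not give. Someone might infer from the choice of parity and age that the plan calls them prognostic. It does not; it only says they will be adjusted for.
- The power margin is not quite zero. The article says "We expect a maximum of 5% to be lost to follow-up, leading to a total of 129 women needed to be enrolled in each group", and LOS comes from medical records, so losses may be smaller than allowed for. With all 129 per group analysed, unadjusted power is 82.1%, about the same as the gain at R² = 5%.
- Swapping the two labels does not prevent the two analyses from disagreeing. Both would still be reported, and the article already makes clear which one governs.

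What the reply does not answer is why the less precise of two planned analyses should be primary if the covariates matter, when the cost is negligible if they do not.

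**Conclusion.** The point holds as a modest efficiency improvement. At 123 per group it is worth between nothing and about 6 points of power for R² between 0 and 15%, and 2 points or less if R² is 5% or below. It assumes a linear model on log LOS and the planning values of 0.75 and 0.80. The same-ratio argument carries over to a log-link count model if the plan switches to one. It does not carry over to the comparison of the proportion with 3 or fewer days in hospital if that is analysed by logistic regression.

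Two stronger readings are tempting and are not supported. A reader might infer that the trial forfeits planned power. It does not, because it was sized for the unadjusted test. A reader might also infer that nonstratified allocation makes the unadjusted result biased or unreliable. It does not, because the test is valid under randomization and plausible chance shifts are small beside the planned effect.

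**What to change.** In the Data analysis section, name the linear model of log LOS on arm, parity and age as the primary analysis, and the unadjusted comparison as supportive. State how the covariates enter, for example parity as nulliparous or parous and age as continuous. The sample size can stay as it is.

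The cost is a short documented amendment; no new data are needed. It should be dated before any unblinded analysis. The Trial status section reports 130 of the planned 258 women included by 22 May 2019 and no interim analyses, and the trial statistician is blinded to allocation, so the change can still be made without knowledge of results.

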### Aim

The aim of this RCT, the ChroPreg Trial, is to evaluate the efficacy of a midwife-coordinated, individualized, and specialized maternity care intervention as an add-on to standard care for pregnant women with chronic diseases. The primary outcome is LOS measured in days of hospitalization from study inclusion until 2 weeks after delivery. Secondary outcomes are patient-reported psychological well-being, health-related quality of life, satisfaction with care, antenatal contacts, and pregnancy and delivery outcomes.

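### For patient-reported scales that have a pre-randomization score, the analysis section gives that score no role, at a cost in precision only

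*Protocol article*

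**What the plan says.** The Data analysis section sets out covariates for length of stay (LOS) only. The log-transformed days in the two groups "will be compared in the primary unadjusted analysis, and in a secondary analysis, adjustments will be made for parity and age". The model is a general linear model, or a generalized one if that fits the counts better. The remaining outcomes get one sentence: "Comparison of secondary and exploratory outcomes will similarly be performed using the general or generalized linear models as appropriate". No baseline score is mentioned, either as included or as excluded.

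The Outcome measures section says that data "will be obtained at baseline (t1) and three times during the study period". On timing it adds: "The participants will complete the first electronic questionnaire after signing the informed consent to participate and before randomization".

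The Aim section lists what the analysis sentence has to cover: "Secondary outcomes are patient-reported psychological well-being, health-related quality of life, satisfaction with care, antenatal contacts, and pregnancy and delivery outcomes". The text does not list the instruments in the baseline questionnaire. The schedule is in Fig. 2, which is not available here.

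**The concern.** An unadjusted comparison followed by adjustment for parity and age suits LOS, because counting starts at inclusion and no baseline value can exist. It suits less well a scale that the same woman has already completed before allocation. A pre-randomization score on the same scale is a valid covariate, and where it correlates with the later score it removes outcome variance that the unadjusted comparison leaves in.

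The Hypothesis section expects better psychological well-being and health-related quality of life, but the sample size was set by LOS alone. Precision for the WHO-5, EPDS, CWS and SF-12 therefore follows from a calculation made for another outcome. At stake are the width of the intervals and the power for these secondary outcomes. The validity of the trial is not in question.

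**Working it through.** **The plan's own figure.** The sample size section gives the inputs: "With a difference of 0.29 and SD of 0.80, a power of 0.8, and a significance level of 0.05", and the result: "an analysis by two-sample *t* test requires 123 women in each group". Taking the test as two-sided (an assumption) and the unrounded effect −log(0.75) = 0.2877:

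- Normal approximation: n = 2 × (1.960 + 0.842)² × (0.80 / 0.2877)², which rounds up to 122 per group.
- Exact two-sample t test: 122.4, rounded up to 123 per group.

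The stated 123 reproduces. It concerns log LOS, so baseline adjustment of questionnaire scores leaves it unchanged.

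**Inputs for the patient-reported scales.**

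- Evaluable women: 123 per arm, taken from the LOS calculation. Questionnaire response may differ, but the percentage narrowing below does not depend on n.
- Baseline to follow-up correlation r: not in the document. It is assumed here over 0.2 to 0.7.

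**Formulas.** For a continuous score in a linear model with the baseline score as covariate:

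- variance factor = 1 − r²
- interval width multiplier = √(1 − r²)
- equivalent unadjusted n per arm = 123 / (1 − r²)
- smallest standardized difference detectable with 80% power = (1.960 + 0.842) × √(2/123) × √(1 − r²) = 0.357 × √(1 − r²)

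Example at r = 0.5: 1 − 0.25 = 0.75; √0.75 = 0.866, so the interval is about 13% narrower; 123 / 0.75 = 164; 0.357 × 0.866 = 0.309.

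| Assumed r | Variance factor | Width multiplier | Interval narrower by | Equivalent n per arm | Detectable difference (SD) | Power for 0.30 SD |
|---|---|---|---|---|---|---|
| unadjusted | 1.00 | 1.00 | – | 123 | 0.357 | 65% |
| 0.2 | 0.96 | 0.98 | 2% | 128 | 0.350 | 67% |
| 0.3 | 0.91 | 0.95 | 5% | 135 | 0.341 | 69% |
| 0.5 | 0.75 | 0.87 | 13% | 164 | 0.309 | 78% |
| 0.6 | 0.64 | 0.80 | 20% | 192 | 0.286 | 84% |
| 0.7 | 0.51 | 0.71 | 29% | 241 | 0.255 | 91% |

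The 0.30 SD difference only illustrates power; the document states no target effect for any scale.

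**Where the formula does not reach.** Antenatal contacts and delivery outcomes have no baseline counterpart. Neither does the PCQ, which includes "birth-related items (7 items") and could not be scored in full at inclusion in weeks 12 to 19. Nor does the formula apply to EPDS dichotomized at its cutoffs. Adding a prognostic covariate to a logistic model generally increases the standard error of the log odds ratio and changes the estimand to a conditional odds ratio.

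**The case against.** The strongest reply is that the article does not rule out baseline adjustment. *Similarly* can be read as referring only to the class of model, and a linear model with a baseline covariate is a general linear model. An article also condenses a fuller plan, and covariates for individual secondary scales often stand there. This limits the point: a reader might infer that the trial has decided to ignore the baseline scores, and the text does not support that. What remains is that the section does address covariates, names parity and age and no others, and carries the approach over to the secondary outcomes. Someone following it as written would leave the baseline scores out.

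A second reply is that the baseline instruments are not listed in the text. This stands, so the point covers the four instruments only as far as they are in that questionnaire.

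A third is that the correlation may be low. Baseline falls in weeks 12 to 19 and the last follow-up is 2 months after delivery, with childbirth in between. This also stands, and it is why the range starts at 0.2, where the gain is negligible.

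Two further inferences are tempting and should not be drawn. One is that every secondary interval is wider than it need be; outcomes with no baseline are unaffected. The other is that nonstratified allocation makes the unadjusted estimates faulty. Stratifying on other factors would not in general balance these scores, and the randomized comparison is unbiased without it.

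**Conclusion.** The point holds in a limited form. The only covariates named are parity and age, and the pre-randomization scores are given no role, although they are collected. The consequence is lost precision on continuous patient-reported scales that have a baseline value. Bias, the primary analysis and the sample size are not affected.

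The interval would be about 2% narrower at r = 0.2, 13% at r = 0.5 and 29% at r = 0.7. The gain is thus trivial at the low end and material from about 0.5 upwards. These figures assume a linear relation between baseline and follow-up, the same variance and slope in both arms, and values of r that are not from the document.

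**What to change.** Add one sentence to the analysis of secondary outcomes. For each continuous patient-reported scale in the baseline questionnaire (as far as they are included: WHO-5, EPDS total score, CWS, and the SF-12 physical and mental component summaries), the main analysis at each follow-up where the scale is collected is a linear model of the follow-up score on treatment group and the baseline score of the same scale. Parity and age stay in the secondary adjusted analysis, as planned. Outcomes with no baseline (PCQ, antenatal contacts, delivery outcomes) are analysed as now written, and the EPDS cutoff analyses are not part of this change. If a separate analysis plan already specifies this, a reference to it is enough.

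The cost is wording only: no added data, visits or participants. The Trial status section reports 130 of the planned 258 women included by 22 May 2019 and no interim analyses, so at that date the covariate could still be fixed before any comparison of the groups.
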